### Intervention

#### Theoretical background

Our intervention relies on models of Social Influence [23,61] and Motivational Interviewing [22], which have proven effectiveness in prior relevant research [34,62]. As described earlier, Motivational Interviewing is a client-centered, non-judgmental, non-confronting approach to decrease drinking and drinking-related consequences [22], which is well-suited for adolescents [63,64]). The goal of an MI approach is to enhance motivation to change by exploring and resolving ambivalence about current substance-related behaviour. Important elements are the presentation of discrepant personal information by providing individualised feedback about substance consumption behaviour. The latter will be relative to normative comparisons in our intervention, balancing pros and cons of the target behaviour and supporting self-efficacy. Provision of individualised feedback regarding risk-status and normative feedback relative to a relevant comparison group figure prominent in the literature on web-based brief interventions [40] since “tailored” feedback is presumably perceived as more relevant than more general information [28]. Normative feedback involves information about how a specific reference group actually consumes in order to correct adolescents’ “inflated perception” [21] and of the amount the reference group typically consumes. It has been proven effective for reduction of alcohol consumption in young adults in recent meta-analyses [65,66]. For young people, a normative feedback approach may be particularly appealing assuming high levels of curiosity in how their substance consumption compares to their peers [27]. Likewise, an important element of our approach is a focus on substance-related social norms and training on how to avoid social high-risk situations and resist peer pressure (i.e., raising refusal self-efficacy) [31,67]. In line with the social influence hypothesis, which states that one of the most prominent risk factors for substance use in adolescence is the influence of substance using peers [68], targeting peer pressure in brief web based interventions has been integrated in recent web-based interventions for reducing alcohol use among adolescents [28].

#### Description of the intervention

The overarching goal of the intervention is to encourage reduced alcohol consumption and abstinence from any illicit drugs.^d^ The single-session intervention is fully automatised and electronically delivered yet interactive. It works with presenting tailored feedback to the participants’ responses in the earlier assessment (i.e., consumption levels) and provides choice options on how to react to this feedback. This interactivity simulates a face-to face “dialogue”, which aims for an empathic style, avoids argumentation, rolls with resistance and aims at creating a dissonance between actual and desired behaviour and raising self-efficacy. To achieve these goals, our intervention basically consists of three components. First, participants will receive personalised feedback on their substance consumption patterns including the associated risks (related to health and other consequences) and comparisons to a normative reference group. Second, participants engage in interactive MI-based exercises that have been proven effective in prompting readiness to change by encouraging the participant to consider the costs and benefits of their current substance use and actual change. Finally, the intervention will include practical advice concerning alternative behaviour in tempting situations, with a focus on peer resistance skills to raise self-efficacy beliefs and implementation intentions. All components will be described in more detail below. The whole intervention can be completed in approximately 10 to 15 minutes.

##### Feedback

Individualised feedback includes evaluation of consumption patterns (e.g., frequency and quantity of use and binge-drinking) concerning various substances according to the answers given in the assessment part. Risk status for negative consequences associated with drinking, use of illicit drugs, and polydrug use (i.e., combined use of various substances) will be based on the participant’s Alcohol (Drug) Use Disorder Identification Tests (AUDIT-C and DUDIT, see Instruments section below). Furthermore, feedback includes an estimation of the blood-alcohol-concentration (BAC) and information on the associated risks (health and other risks, such as traffic crash, unintended sex etc.) concerning the participants’ heaviest drinking episode during the past 30 days. This value will be based on a measure of *Peak Drinking Quantity*[69] (see *Instruments*) and can be estimated using the Widmark-formula which is sensitive for weight and gender [70]. Finally, participants will receive individualized and graphed feedback regarding the following information: a bar chart comparing the number of glasses of standard alcohol units per week that participants think their peers actually consume (descriptive norms), as well as the participant’s individual levels of drinking, both in relation to comparative data (actual drinking levels) from a reference group. Comparative data (AUDIT-C scores) will be taken from alcohol prevalence estimates found in a nationally representative samples of 18 year old males in Sweden.^e^ Comparative feedback will be available for drinking but not for drugs other than alcohol.

##### Interactive MI-based exercises

Based on the literature on MI [22,71], generally the exercises provided in WISEteens assume that 1) participants may hold certain levels of ambivalence about their current substance use (i.e., they can see the advantages and disadvantages of drinking and/or taking drugs), and 2) if they are willing to make a change they may not know how to make a change or may not be confident that they are able to make a change. Based on this assumption, we use importance and confidence rulers with a short summary and feedback to encourage participants to think about their possible personal reasons for change and explore their personal strengths and their ability to change. Furthermore, we implement a decisional balance [72] to pick up and graphically illustrate potential levels of ambivalence by offering the participants a list of possible pros and cons regarding the decision to change their current substance use [73]. Participants are instructed to choose those statements that apply to them and are presented with the resulting balance sheet of their personal comparative potential gains and losses.

##### Practical Advice (menu of options)

In addition to targeting confidence for change in the exercises described above we will focus on raising self-efficacy for avoiding drinking in social situations and providing practical advice to resist temptations. Similar to the approach of Voogt and her colleagues [28] we will ask participants to select three among 12 provided drinking situations that are chosen as most tempting and rank them (the situations are adapted from the adolescent version of the Drinking Refusal Self-efficacy Questionnaire (DRSEQ-RA) [74]. According to the selection several tips will be offered for each of the selected drinking situations to provide participants with a tool kit necessary for engaging in and maintaining their behavioural goal (that is reduced drinking and / or abstain from illegal drugs). Again, practical advice refers to resistance skills for drinking, but participants are encouraged to apply the advice given (e.g., peer resistance) also for resisting drugs other than alcohol and to avoid risky situations in a similar way.

### The control group: assessment only

The control group will receive no intervention besides the assessment. However, participants in the control group are provided with contact information on suitable counselling service providers to get in touch with in case of severe substance use-related problems. All participants are invited to visit again and participate in follow-up assessment after the evaluation period of the intervention of 3 months.

### Instruments

#### Primary outcomes

The primary outcomes of the study refer to reductions of substance use. As prevalence rates of alcohol are particularly high among youth we distinguish measures for alcohol, which will be the main focus, from those in the broader category of drugs other than alcohol. Specifically we use the Alcohol Use Disorder Identification Test Consumption subscale (AUDIT-C) [75]) for frequency of alcohol consumption, frequency of having five drinks (four for girls) at one occasion (binge drinking), with response options ranging from 1 (*never*) to 5 (*four or more times a week*). Rather than using the third original AUDIT-C item, which measures number of standard drinks consumed per typical drinking occasion (1 = *one or two* to 5 = *ten or more*), and in order to ensure standardised responses across the four participating countries, we use a graphical overview of various types of drinks with the indication to select the number of each drink per typical drinking occasion. This way we can better account for national differences in typical standard drinks while keeping the content of the item. Standard drinks are defined as 10 g ethanol and items are assessed over the past 30 days.

For drugs other than alcohol we analogously use the first three items of the Drug Use Disorder Identification Test (DUDIT) [76] assessing frequency of consumption of drugs other than alcohol, frequency of different types of drugs other than alcohol used at the same occasion (1 = *never* to 5 = *four or more times a week*), and quantity of consumption of drugs other than alcohol on a typical consumption day (1 = *zero* to 5 = *seven or more*).

While changes in AUDIT-C and DUDIT scores are the primary outcome measures, the study includes other behavioural measures as well. From the AUDIT-C indication of frequency, quantity and selection of drinks during the last 30 days we will be able to calculate and possibly observe changes in *Weekly Alcohol Consumption* (in gram), which will be matched against the national recommended limits of each country (e.g., for Germany according to published guidelines this limit is 24gr/week for males and 12gr/week for females [77]. In addition we will measure *Peak Drinking Quantity* by asking participants to indicate the amount of drinks consumed on the occasion on which they drank the most during the last month [69], *Frequency of Drinking to Intoxication* (“*During the past 30 days, how many times have you gotten drunk, or very high from alcohol?*”, with response option ranging from *0* to *9 or more*) [27], and *Typical Weekend Drinking*, following Doumas and Hannah [27] by using a modified version of the Daily Drinking Questionnaire [78] using the following item: “*Given that it is a typical week, please write the number of drinks you probably would have each day”*; (*Monday*_______, *Tuesday*______, etc.). Weekend drinking will be the combined reports for Friday and Saturday.

#### Secondary measures

In addition to the behavioural outcome variables described above we assess a number of potential and theoretically plausible moderator and mediator variables, as well as several cognitive-level outcomes. Specifically, we assess the following moderators: *Age of first use*, *General Psychopathology*, using a short version of the Symptom Checklist (SCL-K 9) [79] and *Child Disclosure*[80], as an indicator of parent–child relationship quality. Positive parent–child relationship is a protective factor for adolescent substance use [81] and has been consistently shown to be related to lower likelihood of adolescent substance use [82] and variables related to adolescent substance use, such as self-control, competence, and peer affiliations [83]. Regarding potential mediators and cognitive outcomes we rely on socio-cognitive constructs based on major psychological models predicting health behaviour change, such as Ajzen’s Theory of Planned Behaviour (TPB) [84], and Prochaska & Di Clemente’s Transtheoretical Model (TTM) [85,86]. Both theories are widely used in clinical practice and health psychology and generalise across many different problem behaviours [87,88]. Specifically, we address *attitudes*, *subjective norms*, *perceived behavioural control*, and *behavioural intentions* as the proximal cognitive antecedents of goal-directed behaviour. Additionally we include a measure of *Implementation Intentions*[89] to address the action planning phase in goal attainment. Implementation intentions are defined as plans that specify the conditions under which target behaviours will be performed and help to ensure that the decision is acted upon [90]. Moreover, we include an algorithm for allocating participants into different *stages of change* concerning their substance use [91-93] hypothesising that progression (such as from precontemplation to contemplation) will be more pronounced in the intervention group compared to the control group. All items are adapted from previous related research.

### Sample size

Sample size is based on a power calculation for detecting a small effect size of *d* = 0.2 according to Cohen [94] . Obviously, our hypotheses are directional with better outcomes expected for the intervention group. Following Cohen’s convention [94] the trial is powered to detect a small effect size of *d* = 0.2 or larger given errors of 1−*β* = .80 and *α* = .05 in a one-sided test [95]. Expecting a worst-case scenario of 50% loss to follow-up rate, we aim to recruit n = 200 participants per country, totalling to 800 respondents (n = 400 per condition).

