Among the limited amount of studies using adolescent samples to our knowledge we are the first to design and test a brief intervention for poly-drug using adolescents in a fully-electronic format. Another strong aspect of the present trial is its multi-centre approach with collected data from four European countries, allowing for international comparisons. Finally, we consider it strength to rely solely on internet recruitment in our target population. This approach matches real conditions and directly tests the external validity of our website should its effectiveness be proven. Note that this procedure deviates from other studies which typically test offline before going online [28,55]. While failure to retain a sufficient proportion of participants for follow-up assessment remains a concern for the evaluation we consider it vital to develop a web-site that will be accepted by our target group.

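### At the plan's own 50% loss, 800 recruits leave 200 per arm: about 64% power for d = 0.2 in a simple two-group comparison, not the stated 80%

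*Protocol article*

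**What the plan says.** The Sample size section of the protocol article gives every input of a standard calculation. The target effect and the claim are that "the trial is powered to detect a small effect size of *d* = 0.2 or larger". The error rates are "given errors of 1−*β* = .80 and *α* = .05 in a one-sided test". The allowance for loss and the recruitment target come in one sentence: "Expecting a worst-case scenario of 50% loss to follow-up rate, we aim to recruit n = 200 participants per country, totalling to 800 respondents", and the same sentence ends by putting 400 in each condition. The Abstract confirms that 400 per group is the number randomised.

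The section gives no separate number of analysable participants, no correlation between baseline and follow-up, and no other allowance that would offset the loss. The outcome is measured once after baseline, at three months.

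**The concern.** The sentence that names the 50% loss is the one that sets the target of 800, so a reader takes 800 as a number that already allows for that loss. On the stated inputs it does not, and the gap is large.

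In the scenario the sponsor says it planned for, a true effect of the target size would be missed about 36% of the time, where the plan implies 20%. A null result could then be taken as evidence from an adequately powered trial. Heavy loss is not remote either: the Recruitment section provides a sweepstake to raise follow-up rates, and the Discussion concedes that "failure to retain a sufficient proportion of participants for follow-up assessment remains a concern".

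**Working it through.** **Inputs** (all from Sample size): d = 0.2; power 0.80 (z = 0.842); alpha .05 one-sided (z = 1.645); loss 50%; 800 recruited, 400 per arm. The section does not name the test. The check uses the simplest reading, an unadjusted comparison of two means on one outcome.

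**1. Trying to reproduce 800**

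n per arm = 2(z_α + z_β)² / d²

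- One-sided: 2(1.645 + 0.842)² / 0.04 = 309.3, so 310 per arm and 620 analysable in total (the t-based solution, 309.8, also rounds up to 310).
- Allowing for 50% loss: 310 / (1 − 0.5) = 620 per arm, **1,240 in total**, or 310 per country.
- With the common mistake of multiplying by 1.5: 465 per arm, 930 in total.
- Two-sided, no loss: 2(1.960 + 0.842)² / 0.04 = 392.6, so 393 per arm and 786 in total.
- Two-sided, 50% loss: 786 per arm, 1,572 in total.

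None of the one-sided routes gives 800. The two-sided figure without loss comes close, but it contradicts both the stated sidedness and the stated loss. Taking the two-sided per-arm figure of 393 as a total and doubling it for loss also gives 786. The document does not say how 800 was obtained, so either explanation is conjecture.

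**2. Power that 800 delivers at 50% loss**

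800 × 0.5 = 400 analysed, 200 per arm. The standard error of d is √(2/200) = 0.1, so d / SE = 2.

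- One-sided: Φ(2 − 1.645) = Φ(0.355) = **0.64** (noncentral t: 0.637).
- Two-sided: Φ(2 − 1.960) = Φ(0.04) = 0.52 (noncentral t: 0.514).
- Smallest effect detectable with 80% power: (1.645 + 0.842) × 0.1 = **0.25** one-sided; (1.960 + 0.842) × 0.1 = 0.28 two-sided.

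**3. How much loss 800 can absorb**

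1 − 310/400 = 22.5%. One-sided power for d = 0.2 by loss rate:

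| Loss | n per arm | Power |
|---|---|---|
| 0% | 400 | 88% |
| 20% | 320 | 81% |
| 22.5% | 310 | 80% |
| 30% | 280 | 76% |
| 40% | 240 | 71% |
| 50% | 200 | 64% |

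**4. Could baseline adjustment rescue the claim?**

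With baseline/follow-up correlation r, the residual SD shrinks by √(1 − r²), so power at 200 per arm is Φ(2/√(1 − r²) − 1.645):

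- r = 0.3: 67%
- r = 0.5: 75%
- r = 0.6: 80%
- r = 0.7: 88%

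Reaching 80% takes r of about 0.6 or more, a value the document does not give.

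**The case against.** Three objections have weight.

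*The 64% is not the power of the planned analysis.* The Statistical analyses section plans a MANCOVA on several alcohol variables, with baseline values and cognitive change scores as covariates. Its power depends on correlations that are not given, and an omnibus multivariate test is not one-sided. If d is on the unadjusted scale and r is 0.6 or more, the stated figures become compatible for a one-sided test of a single outcome. This stands as a limit: the figures fail on the plain reading of the paragraph, not under every conceivable assumption. It does not rescue the paragraph, which claims no gain from adjustment.

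*50% is called a worst case.* Lower loss means higher power, and the shortfall is graded: 76% at 30% loss. This softens the likely consequence. It does not remove the inconsistency, because 800 is presented as the number chosen with that loss in view, and the claim already fails once loss exceeds about 22%.

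*Rewording leaves the risk of a missed effect unchanged.* True. Restating the figures corrects what the trial claims, not what it can detect. Only better retention, more recruits or a justified gain from adjustment would raise the power. The Discussion's remark on retention is a general caution with no figure, so it does not already make this correction.

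**Conclusion.** The point holds. The printed effect size, power, alpha, loss rate and recruitment target do not agree: 80% power for d = 0.2 at 50% loss needs 1,240 randomised, 440 more than the 800 planned. With 800, power in that scenario is about 64%, or 80% for d = 0.25.

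The result rests on a one-sided, unadjusted comparison of one outcome with equal arms, and on analysing only those followed up. It takes no account of the several primary outcomes. Because this is the trial's central power statement and every input is printed, it must be corrected.

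**What to change.** Keep 800 and rewrite the Sample size paragraph so that its numbers agree. Either of these would do:

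- *With 800 randomised and 50% loss to follow-up (200 analysed per arm), the trial has 64% power for d = 0.2, or 80% power for d = 0.25, at one-sided alpha .05.*
- *With 800 randomised, 80% power for d = 0.2 at one-sided alpha .05 holds only if loss to follow-up is 22% or less.*

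If baseline adjustment is meant to recover the power, state the assumed baseline/follow-up correlation and its source, say which outcome it applies to, and recompute on that basis.

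The cost is a reworded paragraph and a less favourable power statement. No extra participants and no change to design or analysis are needed.

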### Statistical analyses

To test the efficacy of WISEteens we address the primary research question whether participation in the intervention leads to a decrease in drinking and / or drug consumption other than alcohol at follow-up after three months compared to those adolescents in the assessment-only control group. The main analysis will follow separate analyses for alcohol and drugs. For alcohol consumption we will run multivariate analyses of covariance (MANCOVA) with intervention condition as the independent variable (intervention vs. control group) on the primary dependent variables frequency and quantity (i.e., number of drinks per typical drinking occasion) of alcohol consumption, frequency of binge drinking (AUDIT-C), reductions in weekly drinking and peak drinking. Baseline alcohol units of these variables and change scores (baseline-follow-up) of motivational (i.e., implementation intentions) and the socio-cognitive constructs (i.e., intentions, attitudes, subjective norms, PBC) based on Ajzen’s Theory of Planned Behaviour (TPB) [84] will be included as covariates. For drug use other than alcohol we will analogously run separate analyses of variance (MANCOVAs) on the primary dependent variables frequency and quantity of drug use (DUDIT-C). In addition, we will test whether socio-demographic variables (age, sex, social class), country of residence (Sweden, Germany, Belgium, Czech Republic), general psychopathology, parent–child relationship, age of first use, and stage of motivation to change moderate the outcomes. Moreover we will explore possible mediated effects of our intervention on the various behavioural measures relying on multiple mediation analysis using the syntax of Preacher and Hayes [96] for SPSS, and test direct and indirect effects in a path model using AMOS 18 [97]. Path Analysis is a multivariate technique specifying relationships between observed variables akin to running several regression equations with the advantage that it allows simultaneous testing of several propositions regarding how constructs are theoretically linked and the directionality of significant relationships within one single model [98].

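### The stated power (d = 0.2, one-sided) does not apply to the planned main test, an omnibus MANCOVA that has no direction and does not by itself show a decrease

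*Protocol article*

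**What the plan says.** The Sample size section gives the basis for the trial's size:

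- Direction: "Obviously, our hypotheses are directional with better outcomes expected for the intervention group".
- Effect: "Sample size is based on a power calculation for detecting a small effect size of *d* = 0.2". No outcome is named, but d describes a difference between two means on one variable.
- Error rates: power of .80 and an alpha of .05, one-sided.
- Attrition: "Expecting a worst-case scenario of 50% loss to follow-up rate", with 800 recruited, 400 per arm.

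The Statistical analyses section gives the main test. It asks whether the intervention leads to a decrease in use. For alcohol, "we will run multivariate analyses of covariance (MANCOVA) with intervention condition as the independent variable". The dependent variables, all called primary, are frequency and quantity of drinking together with "frequency of binge drinking (AUDIT-C), reductions in weekly drinking and peak drinking". Drug use gets an analogous MANCOVA on frequency and quantity.

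The Primary outcomes section draws the line elsewhere. It names changes in AUDIT-C and DUDIT scores as the primary measures and introduces weekly consumption and peak quantity as other behavioural measures. It also says that weekly consumption is calculated from the frequency, quantity and drink-selection answers.

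**The concern.** The power statement and the main analysis describe different tests. The first concerns one mean difference in one direction. The second asks whether any linear combination of five variables separates the arms, and its statistic is a squared distance without a sign.

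Two things follow. The 80% and the one-sided alpha cannot be carried over to the test that will be run. And a significant F does not answer the article's own question about a decrease, because improvement, deterioration and a mixture of the two all enlarge the statistic. The efficacy claim would then have to be read from the individual variables, and two sections disagree on which of those are primary.

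**Working it through.** **Inputs.** From Sample size: d = 0.2, one-sided alpha .05, power .80, 400 per arm, 50% loss, hence 400 × 0.5 = 200 completers per arm. From Statistical analyses: five alcohol and two drug dependent variables. Assumed, because the article does not give them: a common residual correlation ρ between outcomes, and the pattern of effects. Effects are in residual SD units, so no separate gain from baseline covariates is added.

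**The plan's own figure.** n per arm = 2(1.645 + 0.842)²/0.2² ≈ 309.2, so 310, or 620 completers. At 50% loss this means recruiting 620/0.5 = 1,240, so 800 is not reproduced. With 200 per arm the noncentrality is 0.2 × √(200/2) = 2.0 and the power is about Φ(2.0 − 1.645) = 64% one-sided (51% two-sided). The shortfall is a separate matter. The 64% is the like-for-like comparator below.

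**Omnibus test, uniform effect.** For two arms the MANCOVA reduces to Hotelling's T². With p outcomes, D² = p·d²/(1 + (p − 1)ρ), noncentrality (n/2)·D², referred to F with p and 2n − p − 1 df. Here p = 5, n = 200, giving F(5, 394). Ten fewer error df for covariates change nothing material.

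| ρ | D² = 0.20/(1 + 4ρ) | noncentrality | power, 200 per arm | power, 310 per arm |
|---|---|---|---|---|
| 0 | 0.200 | 20.0 | 95% | 99.6% |
| 0.2 | 0.111 | 11.1 | 72% | 91% |
| 0.3 | 0.091 | 9.1 | 62% | 84% |
| 0.5 | 0.067 | 6.7 | 47% | 69% |
| 0.7 | 0.053 | 5.3 | 38% | 57% |

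The one-sided single-outcome test has 64% at 200 per arm and 80% at 310. The two tests break even at ρ of about 0.28 and 0.35 respectively.

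**Other patterns.** In general D² = δ′Σ⁻¹δ. With 200 per arm:

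- Effects 0.30, 0.25, 0.20, 0.15, 0.10 (mean 0.2): 79%, 75%, 82% at ρ = 0.3, 0.5, 0.7.
- One outcome at 0.2, the rest at zero: 29%, 35%, 47%, 71% at ρ = 0, 0.3, 0.5, 0.7.
- Mixed: two outcomes better by 0.2, two worse by 0.2, one unchanged. The effects sum to zero, so D² = 0.16/(1 − ρ). At ρ = 0.5 this is 0.32, the noncentrality is 32, and the test rejects in more than 99% of trials.
- All five worse by 0.2: the same D² as for benefit, so 47% at ρ = 0.5. The stated one-sided test would reject in about 0.01%.

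**Drugs.** With p = 2 and d = 0.2 on both outcomes, 200 per arm: 71%, 53%, 43% at ρ = 0, 0.5, 0.9.

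**Directional mean of the five standardised outcomes.** d = 0.2 × 5/√(5 + 20ρ) = 0.30, 0.26, 0.23 at ρ = 0.3, 0.5, 0.7. Power is 91/83/74% one-sided and 85/73/63% two-sided. If only one outcome moves, at ρ = 0.5, d = 0.2/√15 = 0.052 and the two-sided power is 8%.

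**The case against.** A reader might infer that the MANCOVA simply has lower power than the test in the sample-size section. The documents do not support that. Equal effects on all outcomes are an unfavourable pattern for Hotelling's T² when correlations are substantial. With modestly unequal effects the MANCOVA beats the 64% comparator at every correlation tried, and at ρ = 0.7 its 82% exceeds even the one-sided composite (74%). At low correlation it is ahead with equal effects too. Deriving weekly drinking from frequency and quantity makes high correlation plausible, but the relevant correlation is the residual one after the covariates, and it is not given. Part of any low figure at 200 per arm also comes from the recruitment shortfall.

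A reader might also infer that significance for harm is peculiar to the MANCOVA. It is not: any two-sided test, including the composite at ρ = 0.5 (73%), rejects for harm as often as for equal benefit. What differs is that a single outcome carries a readable sign. With uniform harm the group means would show the direction as well. The real difficulty is a mixed pattern.

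Nor is the absence of a rule for univariate follow-up tests a fault here, since an analysis plan may supply one. And no single outcome is named as the basis for power; that is inferred from the use of d.

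What stands is that the article states both the power basis and the main test, and they do not match.

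**Conclusion.** The point holds as a mismatch, not as a proven loss of power. That the omnibus F has no direction, and so cannot be the one-sided test assumed or by itself show a decrease, follows from the form of the test and needs no assumption. The same applies to the drug analysis. The disagreement over whether weekly and peak drinking are primary can be read directly from the two sections.

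The size is conditional. At 200 completers per arm the power of the alcohol MANCOVA ranges from about 38% to 72% for a uniform d = 0.2 with residual correlation 0.7 down to 0.2, and is about 75 to 82% for the unequal effects tried at correlation 0.3 to 0.7. The stated test has 64%. All of this rests on an assumed common correlation and assumed effect patterns.

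**What to change.** 1. Make the primary alcohol test a baseline-adjusted ANCOVA on one directional outcome. The AUDIT-C consumption score, already named primary under Primary outcomes, is the natural candidate. Its third item has been replaced by a drink count, so state how that item is scored or standardised. The mean of the standardised alcohol outcomes is an alternative.
2. Do the same for drugs with the DUDIT score.
3. Report the signed estimate with a two-sided 95% CI. Move the individual variables, or the MANCOVA, to secondary, and make Primary outcomes and Statistical analyses agree on weekly and peak drinking.
4. Restate the power for the test actually used, at the completers expected.
5. If the MANCOVA is kept as primary, give its power over a stated range of correlations and drop the one-sided claim.

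This costs wording and a new power statement, with no new data. There are two downsides. The stated power will be less favourable: a single outcome at d = 0.2 with 200 per arm has 51% two-sided before any gain from baseline adjustment. And some sensitivity is lost if only one component moves, as the 8% against 47% at ρ = 0.5 shows for the five-outcome mean.
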